### Sample size

This study is powered for the acceptability (positive impression per Likert scale) of MMS using a non-inferiority design. An empirical estimate of the SD is 0.76 based on real data from the non-inferiority of low-dose compared with standard high-dose calcium supplementation in pregnancy trial.^19^ Therefore, allowing for a non-inferiority margin of 0.5 point difference, 90% power and an alpha of 0.025 to accommodate two statistical tests for 60 versus 30 mg MMS and 45 versus 30 mg MMS (0.05/2), we would require a total of 147 women. To account for ~5% of missing or incomplete data (fetal loss, withdrawal etc.), we will therefore recruit 26 women for each of the six treatment sequences. Thus, the total sample size will be 156 participants.

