### Statistical analysis

All primary quantitative analyses will be conducted using an intention-to-treat approach and limited to participants with observed outcome data (complete case). For the primary acceptability outcome, we will test two hypotheses: the mean Likert scale score in the 60 mg arm is non-inferior to the mean Likert scale score in the 30 mg arm; second, the mean Likert scale score in the 45 mg arm is non-inferior to the mean Likert scale score in the 30 mg arm. We will treat the Likert scale score as approximately continuous and use a linear mixed effects model for the analysis. A time-varying MMS formulation treatment indicator will be included as a covariate (treatment), and repeated monthly Likert scale scores from the same woman will share the same random intercept. To account for the crossover design, covariates for the randomised treatment sequence (sequence effect) and the visit month (period effect) will be included in the model.^20^ Two-sided 97.5% CI (to account for multiple comparisons) of the treatment effects will be presented and compared with the non-inferiority margin of −0.5 points. If most responses in the Likert scale concentrate in a few categories, cumulative link mixed models will be used.

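### The stated 90% power with 147 women is not the power of the stated primary test: the figure reproduces at a one-sided 0.025 level, while the two-sided 97.5% confidence interval tests at one-sided 0.0125

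*Protocol article*

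**What the plan says.** The Sample size section of the protocol article gives these ingredients:

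- Level: "an alpha of 0.025 to accommodate two statistical tests for 60 versus 30 mg MMS and 45 versus 30 mg MMS (0.05/2"). It does not say whether this is one- or two-sided.
- Margin and power: "allowing for a non-inferiority margin of 0.5 point difference, 90% power".
- Variability: "An empirical estimate of the SD is 0.76". It does not say whether this is a per-period SD, a within-woman SD or the SD of a difference.
- Result: "we would require a total of 147 women", raised to 156 (26 in each of six sequences) to allow for about 5% incomplete data.

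The Statistical analysis section states the decision rule for the primary outcome: "Two-sided 97.5% CI (to account for multiple comparisons) of the treatment effects will be presented and compared with the non-inferiority margin of −0.5 points". The hypotheses are that 60 mg and 45 mg are each non-inferior to 30 mg on the mean Likert score. The model is a linear mixed model with a random intercept for each woman.

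**The concern.** Both sections justify their level by the same two-comparison adjustment, so a reader expects one level throughout. However, a non-inferiority claim turns on one limit of the interval. A two-sided 97.5% interval leaves 1.25% in the deciding tail, so the analysis tests each comparison at one-sided 0.0125. If the sample size was worked out with 0.025 in that tail, the halving of 0.05 was applied to a one-sided level in one section and to a two-sided level in the other.

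What is at stake is whether the published alpha, N and power describe the primary test. The difference could also show in a result. If the lower limit of a 97.5% interval fell below −0.5 while that of a 95% interval did not, the stated rule would be failed, although the level behind the sample size would be passed.

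**Working it through.** **Inputs.** Margin 0.5, SD 0.76, power 90% (z = 1.2816) and level 0.025 come from the Sample size section. The decision interval comes from the Statistical analysis section. A true difference of 0 is assumed, because the article gives none.

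**1. Reproducing 147.** For two independent groups, the number per group is

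n = 2 × SD² × (z_α + z_power)² / margin²

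| One-sided level | z_α | n unrounded | n per group | × 3 |
|---|---|---|---|---|
| 0.05 | 1.645 | 39.57 | 40 | 120 |
| 0.025 | 1.960 | 48.55 | 49 | **147** |
| 0.0125 | 2.241 | 57.35 | 58 | 174 |

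Written out for the second row: 2 × 0.5776 × (1.960 + 1.2816)² / 0.25 = 48.55. This matches the article exactly. Then 147 / 0.95 = 154.7, so 155, which is rounded up to 156 = 6 × 26.

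Other variants do not return 147. A t-based version at one-sided 0.025 gives 50 per group (150). Paired versions at one-sided 0.025 need between 15 women (within-woman correlation 0.7) and 49 women (correlation 0).

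**2. The level of the stated test.** A two-sided 97.5% interval has 0.025 / 2 = 0.0125 in each tail, so z = 2.241. Over two comparisons the Bonferroni bound is 2 × 0.0125 = 0.025, one-sided.

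**3. Power at that level, on the formula that gives 147.** Power = Φ(margin / (SD × √(2/n)) − z_α).

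- 49 per group: 0.76 × √(2/49) = 0.1535, and 0.5 / 0.1535 = 3.256. With z = 1.960, Φ(1.296) = 90.3%. With z = 2.241, Φ(1.015) = 84.5%.
- 52 per group (156 / 3): 86.7% with z = 2.241.

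**4. Power of the design actually used.** Every woman takes all three formulations, so each comparison uses all the women. With per-period SD 0.76 and within-woman correlation ρ, the standard error of a treatment difference is 0.76 × √(2(1 − ρ)/N). The article does not give ρ, so a range is shown, all at one-sided 0.0125.

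| ρ (assumed) | Women needed for 90% | Power, N = 147 | Power, N = 156 |
|---|---|---|---|
| 0 | 58 | 99.97% | 99.98% |
| 0.3 | 41 | >99.99% | >99.99% |
| 0.5 | 29 | >99.99% | >99.99% |
| 0.7 | 18 | >99.99% | >99.99% |

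For ρ = 0 and N = 147: 0.76 × √(2/147) = 0.0886, 0.5 / 0.0886 = 5.640, and 5.640 − 2.241 = 3.399, so Φ = 0.9997. If 0.76 is the SD of a within-woman difference, the ρ = 0.5 row applies. If it is the within-woman SD, the ρ = 0 row applies.

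**The case against.** **The levels agree at face value.** A level of 0.025 and a 97.5% interval are complements, and the natural reading is a two-sided 0.05 split over two comparisons in both sections. The article nowhere says one-sided. It stands that the one-sided level is inferred from the arithmetic. It does not remove the problem: read as two-sided, 0.025 agrees with the interval, but 147 then no longer follows from the formula that returns it. Neither reading brings level, N, power and decision rule into line under that formula.

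**Another route to 147 is possible.** A paired calculation at one-sided 0.0125 with zero within-woman correlation detects (2.241 + 1.2816) × 0.76 × √(2/147) = 0.312 points with 90% power, so an assumed true difference of about −0.19 would also give about 147 women. This shows that the reconstruction is not the only conceivable one. The article states no such difference, and the parallel-group formula matches without one.

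**A reader might infer that type I error is in doubt or inflated.** The article does not support that. The error rate is fixed by the decision rule, which the Statistical analysis section states in full: one-sided 0.0125 per comparison and at most 0.025 over both. The level used for sizing cannot alter it, and the rule is the stricter of the two.

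**A reader might infer from 84.5% or 174 that the trial is too small.** That does not follow either. Those figures belong to a three-arm parallel trial. They show only that the stated power and the stated test do not match.

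**Conclusion.** Wrong as written. The 90% power quoted for 147 women is not the power of the test that will decide the primary outcome. On the formula that reproduces 147, that test would have 84.5% power, and 90% would take 174 women. In the crossover itself its power is above 99.9%, even at zero within-woman correlation.

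The match to 147 rests on the z-based formula for three parallel groups with a true difference of 0. The crossover figure rests on 0.76 being the per-period SD and on a true difference of 0. Within those limits, the point is a sample-size justification that needs restating. It leaves the size of the trial and its error control as they are.

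**What to change.** 1. Keep the two-sided 97.5% interval and the −0.5 margin in the Statistical analysis section. That rule already fixes the error rate.
2. In the Sample size section, give the level as one-sided 0.0125 per comparison, 0.025 overall.
3. Replace the power statement with one computed at z = 2.241 from the crossover (within-woman) variance. Say what the SD of 0.76 measures, and give the assumed true difference and within-woman correlation. With 0.76 as the per-period SD, a true difference of 0 and correlation 0, the power is 99.97% with 147 women and 99.98% with 156.

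This costs a few lines of text. N does not change, and recruitment was completed on 23 January 2026. The correction is best recorded before the unblinded analysis. The article expects follow-up to end in late June 2026.

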**Methods and analysis:**

The Multiple Micronutrient Supplementation (MMS) Iron Dose Acceptability Crossover Trial is an individually randomised, quadruple-blind, non-inferiority crossover trial of daily antenatal MMS supplementation formulations that contain 60 mg, 45 mg and 30 mg elemental iron among pregnant women in Dar es Salaam, Tanzania. A total of 156 pregnant participants will be randomised to a sequence in which they receive each of the three MMS formulations for 1 month. Participants, investigators, outcome assessors and data analysts will be blinded to the treatment sequence. The primary trial outcome is participant-reported acceptability of each MMS formulation, measured on a Likert scale. Secondary and tertiary outcomes include preferred and least preferred formulation, identification of MMS formulation, reported side effects and adherence assessed by pill count. Regression analyses will be used to assess differences between formulations and will account for sequence and period effects of the crossover trial design. Qualitative in-depth interviews from a subsample of participants will be conducted to understand women’s perceptions and experiences taking the different MMS formulations.

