## Methods and analysis

The Multiple Micronutrient Supplementation (MMS) Iron Dose Acceptability Crossover Trial (MID-ACT) is an individually randomised, quadruple-blind, non-inferiority crossover trial of daily MMS supplements containing 60 mg, 45 mg or 30 mg of elemental iron among pregnant women in Dar es Salaam, Tanzania (clinicaltrials.gov registration: NCT06069869). The crossover design, in which each participant serves as their own control, was selected to allow for evaluation of within-participant preferences and acceptability, as well as reduce between-person variability to improve statistical power. We will also assess whether or not participants can identify the MMS formulations with higher iron dosages. Trial recruitment started on 26 September 2025 and was completed on 23 January 2026. The follow-up of participants is ongoing and is expected to be completed in late June 2026.

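### The 147 women match a three-arm parallel-group calculation, so the stated 90% power at the 0.5-point margin is not the power of this crossover, which is about 99.97% or more

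*Protocol article*

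**What the plan says.** The Methods and analysis section of the protocol article describes a three-formulation crossover: "The crossover design, in which each participant serves as their own control". It gives two reasons for this choice: to study preference and acceptability within the same woman, "as well as reduce between-person variability to improve statistical power". The Abstract confirms that participants are "randomised to a sequence in which they receive each of the three MMS formulations for 1 month".

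The Sample size section states its inputs as follows:

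- "An empirical estimate of the SD is 0.76", taken from a trial of calcium supplementation in pregnancy;
- "allowing for a non-inferiority margin of 0.5 point difference";
- "90% power and an alpha of 0.025 to accommodate two statistical tests".

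From these it concludes that "we would require a total of 147 women", and raises this to 156 (26 in each of six sequences) for about 5% missing data. It does not name a formula, the kind of SD, a within-woman correlation or an assumed true difference.

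The Statistical analysis section fits a linear mixed model to all three monthly scores, with a random intercept per woman and terms for sequence and period. It compares a two-sided 97.5% confidence interval with −0.5.

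**The concern.** The sample size appears to price a trial in which each woman takes one formulation, whereas the trial gives her all three and compares her with herself. If so, the calculation credits neither the threefold data per formulation nor the within-woman correlation, although power is one of the protocol's reasons for choosing a crossover.

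Two things are at stake. First, the stated 90% power is not a property of this design, so a reader would misjudge its precision. Second, the actual precision allows a result that the parallel calculation would exclude: an interval that clears −0.5 yet lies wholly below zero. A higher-iron formulation would then be both non-inferior and significantly less acceptable than 30 mg. The analysis section does not say how that would be worded.

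**Working it through.** **Inputs from the document.** SD 0.76; margin 0.5; power 90% (z = 1.2816); alpha 0.025 in the Sample size section (z = 1.960 if one-sided). The planned two-sided 97.5% interval implies one-sided 0.0125 (z = 2.2414).

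**Assumptions.** True difference 0; 0.76 is the SD of a single score; within-woman correlation ρ between 0 and 0.7.

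**Step 1: reproduce the stated figure.** Independent groups, per arm:

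2 × (1.960 + 1.2816)² × 0.76² / 0.5² = 48.55, so 49. Three arms: 3 × 49 = 147, an exact match. Then 147 / 0.95 = 154.7, so 155, rounded up to 156 = 6 × 26.

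Variants of the parallel formula give other totals: one-sided 0.0125, 58 × 3 = 174; one-sided 0.05, 40 × 3 = 120; two arms only at one-sided 0.025, 98.

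**Step 2: size the crossover.** Total women N = 2 × 0.76² × (1 − ρ) × (z_α + z_β)² / 0.5².

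| ρ | N, one-sided 0.025 | N, one-sided 0.0125 |
|---|---|---|
| 0 | 49 | 58 |
| 0.3 | 34 | 41 |
| 0.5 | 25 | 29 |
| 0.7 | 15 | 18 |

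If 0.76 were the SD of paired differences, the result equals the ρ = 0.5 row. Using the t distribution adds about two or three women. Even the extreme ρ = −1 gives only 98 or 115. A crossover N of 147 would need a true deficit of about 0.19 to 0.30, or an SD of about 1.2 to 1.9. The document states neither.

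**Step 3: power with 147 women.** SE of a contrast = 0.76 × √(2(1 − ρ)/147); power = Φ(0.5/SE − z_α).

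| ρ | SE | Power, one-sided 0.0125 |
|---|---|---|
| 0 | 0.0886 | 99.97% |
| 0.3 | 0.0742 | above 99.99% |
| 0.5 | 0.0627 | above 99.99% |
| 0.7 | 0.0486 | above 99.99% |

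At one-sided 0.025 and ρ = 0, power is 99.99%.

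**Step 4: can an interval clear −0.5 and lie wholly below 0?** The half-width is h = 2.2414 × SE, so the observed deficit must lie between h and 0.5 − h.

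- Parallel, 49 per arm: SE = 0.76 × √(2/49) = 0.154 and h = 0.34. The deficit would have to exceed 0.34 and be below 0.16, which is impossible.
- Crossover, ρ = 0: h = 0.20; deficits of about 0.20 to 0.30.
- Crossover, ρ = 0.5: h = 0.14; deficits of about 0.14 to 0.36.

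**The case against.** **The error is in the safe direction.** This stands. Power exceeds the stated figure, and the margin, model and test are unaffected. A reader might infer that the trial is underpowered or its primary analysis invalid; the figures show the opposite.

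**The formula is not stated.** This also stands, in part. The parallel-group origin is inferred from an exact match and is not documented, and a condensed article may omit detail. The omission does not rescue 147, because a crossover reaches it only with an undisclosed true deficit or a much larger SD. Nor does the article say that the number was deliberately conservative or meant for a first-period comparison, and it plans no such comparison.

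**A result that is both non-inferior and significantly worse arises from margin and precision, not from the formula.** Correct: a properly written paragraph with 156 women and a 0.5 margin would leave the same region. The interval will be presented, and preference, side effects and adherence are also analysed, so a deficit would not be hidden. What is missing is an agreed wording for it.

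**The margin.** A reader might infer that 0.5 is wrong, or that a tighter margin such as 0.3 should be added because the design can resolve it. The documents do not support that. A margin rests on the loss judged acceptable, and achievable precision alone does not justify one.

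**Mixed alphas.** The 147 reproduces at one-sided 0.025, whereas 58 and 29 use the 0.0125 implied by the planned interval. The like-for-like crossover figures are 49 and 25. The two sections disagree on alpha, and this needs correcting too: on the parallel formula at 0.0125, 49 per arm would give 84.5% power.

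**Model.** The power figures apply to the linear model. The fallback cumulative link model has no direct counterpart to a 0.5-point margin.

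**Conclusion.** The point holds as a moderate correction to the sample-size justification. The stated 147 women for 90% power is what a three-arm parallel trial would need on the given inputs. With zero true difference, no crossover calculation on those inputs gives it.

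For the crossover as planned, power at 0.5 is about 99.97% or more at one-sided 0.0125, and about 99.99% or more at one-sided 0.025, for any non-negative correlation. Even at ρ = −0.5 it is 99.1% at one-sided 0.0125. The number needed for 90% falls from about 58 (ρ = 0) to 29 (ρ = 0.5) at 0.0125, or from 49 to 25 at 0.025.

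This rests on 0.76 being the SD of a single score and on a true difference of 0. Reading 0.76 as the SD of paired differences leaves the conclusion unchanged.

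**What to change.** Recruitment is complete, so N stays at 156.

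1. Rewrite the Sample size paragraph for the crossover. State which SD 0.76 is, the assumed within-woman correlation and true difference, and one alpha that agrees with the planned 97.5% interval. Give the resulting power at 0.5 and the expected precision (SE about 0.05 to 0.09 with 147 women). If the parallel formula was used deliberately, say so and why.
2. While analysts are still blinded, add one sentence to the analysis plan: an interval above −0.5 but wholly below 0 will be reported as *lower acceptability, within the margin*, and not as non-inferior without qualification.

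No second margin is needed. The cost is one rewritten paragraph and one added sentence, with no further participants, data or change to the primary test.

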### Statistical analysis

All primary quantitative analyses will be conducted using an intention-to-treat approach and limited to participants with observed outcome data (complete case). For the primary acceptability outcome, we will test two hypotheses: the mean Likert scale score in the 60 mg arm is non-inferior to the mean Likert scale score in the 30 mg arm; second, the mean Likert scale score in the 45 mg arm is non-inferior to the mean Likert scale score in the 30 mg arm. We will treat the Likert scale score as approximately continuous and use a linear mixed effects model for the analysis. A time-varying MMS formulation treatment indicator will be included as a covariate (treatment), and repeated monthly Likert scale scores from the same woman will share the same random intercept. To account for the crossover design, covariates for the randomised treatment sequence (sequence effect) and the visit month (period effect) will be included in the model.^20^ Two-sided 97.5% CI (to account for multiple comparisons) of the treatment effects will be presented and compared with the non-inferiority margin of −0.5 points. If most responses in the Likert scale concentrate in a few categories, cumulative link mixed models will be used.

Preference between two doses (45 mg vs 30 mg, and 60 mg vs 30 mg) will be analysed using the win ratio method to determine the preferred dose among each dose pair based on the preference of each participant. We collected the participants’ preferences for MMS formulations with 30 mg, 45 mg or 60 mg of iron by asking which supplement they liked the most or the least after taking all three MMS formulations. Take the 30 mg vs 60 mg comparison as an example. Logistic regression will be employed to estimate the probability that the 30 mg regimen is the preferred one among the two regimens for a specific woman, adjusting for differences in the periods of the 30 mg regimen and the 60 mg regimen, as well as the sequence of the three regimens (six sequences in total using five binary indicators). The sample size will be the number of pregnancies that received both the 30 mg and the 60 mg formulation. We will report the point estimate and 95% CIs for the percentage of participants favouring the 30 mg method as the winner. If the preference is not different between the 60 mg and the 30 mg formulations, the percentage of pregnancies choosing the 30 mg regimen as the winner should equal 50%. Similar analyses will be performed to compare 45 mg versus 30 mg.

Percent adherence will be modelled as a continuous outcome with a similar approach to the continuous Likert score outcome. A linear mixed effects model will be used with a time-varying covariate for MMS formulation (treatment), covariates for the sequence effect and period effect with random effects to account for repeated measures for each participant. For binary side effect outcomes (any side effect in the past month and individual symptom side effects reported in the past month), we will use log-binomial generalised estimating equation (GEE) models with MMS formulation as a time-varying covariate with covariates for sequence and period effects. Repeated measures within participants will be accounted for using the GEE model. We will assess differences in the number of days during the prior month that any side effect, as well as individual symptoms, was reported using GEE models with a log link and Poisson distribution. MMS treatment will be included as a time-varying exposure, with covariates for sequence and period effects, and will account for repeated measures. We will consider the adjustment of gestational age at the study visit and baseline side effects to potentially reduce extraneous variation and increase power.

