### Data collection

Participants will have a baseline, 1-month follow-up, 2-month visit and 3-month visit (discharge). The schedule of assessments by visit is presented in figure 1. At baseline, participants will have sociodemographic characteristics assessed. Height will be measured by a stadiometer at the baseline visit. Maternal weight and mid-upper arm circumference will be taken at each study visit. At baseline and during pregnancy follow-up visits, participants will be seen by a study nurse, who will ask about their medical history and receive a clinical examination. Participants will be asked to recall morbidities, symptoms and side effects in the last 28 days at all visits. The Patient Health Questionnaire-9 and Functional Assessment of Chronic Illness Therapy (FACIT)-Fatigue Scale will be used to assess depression and fatigue symptoms, respectively, at all study visits.^15 16^ At each follow-up visit, study staff will take a pill count of tablets returned in MMS blister packs to assess adherence and participants will be asked about the acceptability of the MMS formulation they took in the last month, the primary trial outcome, using a continuous Likert scale ranging from 1 (disliked a lot) to 5 (liked a lot) to capture general impressions.

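### The ordinal-model fallback for the primary outcome has no margin: if it is triggered, the comparison with −0.5 points cannot be made as written

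*Protocol article*

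**What the plan says.** All references are to the protocol article.

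- **Statistical analysis.** Two primary hypotheses are stated, 60 mg against 30 mg and 45 mg against 30 mg. Each says that the mean score on the higher dose is non-inferior to the mean score on 30 mg. The score is treated as approximately continuous in a linear mixed model with a random intercept per woman and terms for treatment, sequence and period. The decision rule is: "Two-sided 97.5% CI (to account for multiple comparisons) of the treatment effects will be presented and compared with the non-inferiority margin", which is set at −0.5 points.
- **Same paragraph, last sentence.** "If most responses in the Likert scale concentrate in a few categories, cumulative link mixed models will be used". The sentence does not define most or few, does not name a link function, gives no margin for the new model, and does not call that model supplementary.
- **Sample size.** The plan is based on "allowing for a non-inferiority margin of 0.5 point difference, 90% power and an alpha of 0.025". On variability it says: "An empirical estimate of the SD is 0.76 based on real data", the data being those of a calcium supplementation trial in pregnancy.
- **Data collection.** Acceptability is measured "using a continuous Likert scale ranging from 1 (disliked a lot) to 5 (liked a lot").
- **Randomisation and blinding.** Data analysts are blinded to treatment sequence.

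**The concern.** The hypotheses, the margin and the decision rule are all in points on the mean score. The fallback model has a different target, an odds ratio conditional on the woman's random intercept. A confidence interval for that quantity cannot be set against −0.5 points. Followed literally, the last sentence of the paragraph therefore removes the comparison that the rest of the paragraph defines, for the trial's only primary outcome. The team would then have to choose either an odds-ratio margin or a method of conversion once the score distribution is known.

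This matters in practice only if the switch is a realistic prospect, so the planning SD has to be examined as well.

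**Working it through.** **1. The plan's own figure.** Inputs from Sample size: margin 0.5, SD 0.76, power 90%, alpha 0.025. Taking no true difference and alpha as one-sided,

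n per arm = 2 × SD² × (z₀.₉₇₅ + z₀.₉₀)² / margin² = 2 × 0.5776 × (1.960 + 1.282)² / 0.25 = 48.6, rounded up to 49.

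3 × 49 = 147, which is the stated requirement. So 0.76 entered the formula as the SD of a single score, in the same points as the margin.

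**2. How concentrated are scores with SD 0.76?** Assume whole-number scores from 1 to 5. Linear programming over every distribution on those scores with SD 0.76 gives the smallest possible share in the fullest categories:

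| | Smallest possible share | Distribution attaining it |
|---|---|---|
| Two fullest | 71% | 0.2888, 0.4224, 0.2888 on scores 3, 4, 5 |
| Three fullest | 88% | 0.0578 on each of 1, 2, 4, 5 and 0.7690 on 3 |

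Both have the right variance: 2 × 0.2888 × 1² = 0.5776 = 0.76², and 2 × 0.05776 × (1² + 2²) = 0.5776. Rounded normal distributions with SD 0.76 and means from 3.0 to 4.5 give 74–88% in two categories and 92–98% in three. For contrast, a uniform spread over five scores has SD √2 = 1.41, with 40% in two categories and 60% in three.

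**3. What odds ratio equals a 0.5-point fall?** Take the rounded normal with mean 4.0: shares of about 0, 0.022, 0.222, 0.490 and 0.266 on scores 1 to 5. The cumulative shares at scores 2, 3 and 4 are 0.022, 0.244 and 0.734. Adding 1.227 to each cumulative logit turns these into about 0.071, 0.524 and 0.904. With the share at score 1 still close to 0, the new mean is 1 + 1 + 0.929 + 0.476 + 0.096 = 3.50, a fall of 0.5. The log odds ratio is −1.227. Repeating this for other reference means:

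| Reference mean | Marginal log OR for −0.5 points | OR | Inverted |
|---|---|---|---|
| 3.0 | −1.273 | 0.280 | 3.57 |
| 3.5 | −1.274 | 0.280 | 3.58 |
| 4.0 | −1.227 | 0.293 | 3.41 |
| 4.25 | −1.179 | 0.307 | 3.25 |
| 4.5 | −1.143 | 0.319 | 3.14 |

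In the other direction, a fixed marginal odds ratio of 0.30 would mean a fall of 0.47 points at mean 3.5 and 0.53 points at mean 4.5.

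**4. The mixed model reports a conditional odds ratio.** The usual logistic-normal approximation is: conditional log OR ≈ marginal log OR × √(1 + 0.346v), where v = 3.29 × ICC / (1 − ICC). The article gives no ICC, so I assume a latent ICC of 0.3 to 0.5.

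- ICC 0.3: v = 1.41, factor 1.22. The log ORs −1.274 and −1.143 become −1.554 and −1.394, so OR 0.21 to 0.25.
- ICC 0.5: v = 3.29, factor 1.46. They become −1.863 and −1.671, so OR 0.16 to 0.19.

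The same half point thus maps to a conditional OR between about 0.16 and 0.25. Most of this spread comes from a variance that is unknown until the data are in.

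**5. Does the mean-score analysis need replacing?** Within-woman linear analyses were simulated with five-category scores, SD 0.76, 147 women, a two-sided 97.5% interval, latent correlation 0.3 or 0.6, and 6,000 trials per setting. The nominal one-sided error is 1.25%.

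| Reference mean | One-sided error at a true difference of −0.5 |
|---|---|
| 3.5 | 1.2–1.4% |
| 4.0 | 1.4% |
| 4.25 | 1.6% |
| 4.5 | 1.85% |

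Power at no true difference was about 100% throughout. In a separate simulation with 55% of responses at score 5 (20,000 trials per setting), the error was 1.6–1.8% with a pooled variance and 1.4–1.5% with a robust variance.

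**The case against.** The strongest reply has four parts.

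*An ordinal model is a respectable choice for scores near a ceiling, and the simulations show some inflation there.* True. But the inflation is a fraction of a percentage point and a robust variance removes part of it. That does not justify giving up the scale on which the margin is defined.

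*The article is condensed, so the trigger and the conversion may be in the SAP.* A missing threshold alone would be no finding. The point is that the article states a rule which, followed as written, conflicts with the hypotheses and margin in the same paragraph. A supplementary role for the model is conceivable, but the wording does not say so.

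*The concentration figures rest on assumptions.* They do. Data collection calls the scale continuous, although the trigger itself presupposes categories. The SD comes from another trial, and the article does not say that it was measured on the same scale. The three-category share is also weak evidence, because any five-category distribution puts at least 60% in three. The two-category share carries the argument.

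*Marginal odds ratios of 3.1 to 3.6 vary little.* Also fair. The larger variation is in the conditional odds ratio, which is what the model reports, and that range depends on an assumed ICC.

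Three stronger conclusions that a reader might draw are not supported:

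- **That the switch is almost certain.** No threshold is given, so no probability can be computed. A strict rule, such as more than 90% in two categories, would not be met by the rounded normals above.
- **That no margin could be fixed in advance.** Fitted ordinal probabilities can be standardised to a mean-score difference, and −0.5 then applies. The article just does not say so.
- **That the error rate is uncontrolled.** The trigger concerns the distribution of responses, not a treatment contrast, and analysts are blinded to sequence. The error of the switching procedure was not simulated. Blinding limits a treatment-directed choice, but it does not supply a margin.

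**Conclusion.** The point holds. The fallback sentence replaces the model for the primary outcome with one whose estimate cannot be compared with −0.5 points as the article stands, and no fixed odds ratio is equivalent to that margin. If scores are whole numbers and 0.76 is the SD of single scores on this 1–5 scale, at least 71% of responses fall in two categories and 88% in three. On an ordinary reading the switch is then likely, and more cannot be said without a threshold. The consequence is an undefined primary comparison if the switch occurs. It is not a demonstrated loss of error control, and the margin can be recovered by a conversion specified in advance. The sample size of 147, recruited as 156, is not affected.

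**What to change.** Amend the Statistical analysis section, or fix the same in the SAP, before unblinding:

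1. The linear mixed model mean difference with its two-sided 97.5% confidence interval, using cluster-robust or bootstrap standard errors, is the sole confirmatory non-inferiority analysis whatever the distribution of scores.
2. The cumulative link mixed model is a sensitivity analysis. Its fit is averaged over the random intercept and standardised over the sample to give a marginal mean-score difference with a bootstrap interval, which is then compared with −0.5 points.
3. The conditional trigger is removed.

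This is a change of wording only, with no new data and no change in sample size. The price is the slight one-sided error inflation near the ceiling, about 1.4–1.9% against 1.25%, with robust standard errors at the lower end. The article expects follow-up to end in late June 2026, so the amendment can be made before the treatment codes are opened.
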